### Study interventions

All study participants will begin the study receiving high-dose amoxicillin divided into three times daily and given orally for 5 days. Doses will vary over a range of 75–100 mg/kg/day within weight strata to simplify medication administration and reduce potential dosing errors. After the first 5 days of amoxicillin, half of the participants will take a second 5 days of amoxicillin dosed identically to the first 5 days (using a different product with a different flavour), and the other half of the participants will be given 5 days of placebo. This placebo will be Ora-Plus (NDC0574-0303-16) produced by Perrigo and distributed by Medisca, mixed with banana flavouring and sugar. No dose adjustments will be made.

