All serious AEs (SAEs) that are both unexpected and related to the study product will be reported to Health Canada, and those related to the study product or procedures will be reported to the appropriate REB as soon as possible if required by the REB, but no later than 15 calendar days (7 days if fatal or life-threatening) after first knowledge of the event. Further information and significant new information on ongoing reported SAEs will be provided to the sponsor, the REB and Health Canada, as applicable. Copies of all information about the SAE will be kept in the regulatory binder.

All caregivers will be asked to complete a symptom diary form each day post-randomization until the tenth post-randomization day; questions on this form will seek information on clinical features of persistent or worsening respiratory disease (e.g. fever, difficulty breathing, overall clinical status) in addition to common (e.g. diarrhoea) and serious (e.g. anaphylaxis) AEs known to be associated with amoxicillin administration. In addition, the RA will specifically ask about symptoms and signs consistent with respiratory deterioration or amoxicillin-associated AEs. This will also be done at the time of visit 1, when the participants return to be clinically evaluated at day 14–21 post-randomization.

The SAE most likely to occur is hospitalization in the first few days post-recruitment, due to worsening respiratory status. Though the majority of children with mild CAP respond well to oral antimicrobial therapy, a small percentage will worsen and require admission to hospital because of progressive oxygenation failure and/or the need for operative drainage of pleural-based collections. These SAEs would not be related to any trial procedures, as all study participants will be receiving the first-line antimicrobial agent of choice (high-dose amoxicillin) for the first 5 days post-enrolment. We note that the risk of harm to trial participants will likely be less than to non-participants, because study staff will be contacting all study participants at intervals to verify clinical stability. As detailed above, the RAs will contact all study participants once at day 3–5 post-recruitment and once at day 7–10 post-recruitment and will be actively questioned about symptoms indicative of worsening respiratory status. Furthermore, all participants that are persistently febrile at day 4 post-recruitment will complete 10 days of open-label high-dose amoxicillin.

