#### Analysis

We will use descriptive statistics to describe the baseline characteristics of the groups reported as count (percent) for categorical variables, and mean (standard deviation) or median (first quartile, third quartile) for continuous variables, depending on the distribution. We will adopt Consolidated Standards of Reporting Trials (CONSORT) criteria for reporting on non-inferiority and equivalence trials in reporting the trial [38]. The principal analysis will be per- protocol, as is recommended for non-inferiority trials [39–41]. The principal analysis is not intention-to-treat (ITT) simply because the effect of ITT analysis is to reduce the difference seen between treatment groups; in a superiority trial, ITT analysis functions to buttress a conclusion of superiority, but in a non-inferiority trial it could lead to a false conclusion of non-inferiority by masking a true difference between treatment arms.

We will use logistic regression to analyze binary outcomes, Poisson regression for count outcomes and linear regression for continuous outcomes. Descriptive analyses will be used to compare rates of viral and atypical co-infections in the entire study population and between groups.

We will perform some subgroup analyses by adding an interaction term between treatment group (5-day vs. 10-day course) and the following subgroups: (1) older (age 5–10 years) vs. younger (age <5 years); (2) higher vs. lower salivary CRP; and (3) virus/*Mycoplasma* detected in baseline NPS vs. no virus detected. These interaction tests will be exploratory in nature and not adjusted for multiple testing [42].

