These analyses will be exploratory. The following sensitivity analyses are planned: (1) intention-to-treat analysis; (2) strict per-protocol analysis including only those participants who were adherent to their medications and whose radiographs were reported by a radiologist to demonstrate alveolar infiltrates; (3) per-protocol analysis stratified by whether the saliva CRP was greater than the 75th percentile; and (4) per-protocol analysis stratified by whether a virus, an atypical pathogen, or high-level *S. pneumoniae* colonization was found in the NPS. If evidence is found of effect modification or confounding related to the above parameters additional analyses will be undertaken. The results of all analyses will be reported as estimate of effect, corresponding 95% CI and associated *p* values. All *p* values will be reported to three decimal places with those less than 0.001 reported as *p* < 0.001. The criterion for statistical significance will be set at alpha = 0.05. Table 1 provides a summary of the outcomes, corresponding hypotheses, measure, and method of analysis.

**Table 1 Tab1:** Variables, measures, and methods of analysis

Variable/outcome	Hypothesis	Outcome measure	Methods of analysis
Primary			
Clinical cure (per-protocol)	Short-course (5-day) treatment with high-dose amoxicillin is non-inferior to long-course (10-day) treatment	At visit (day 14–21) composite of: 1. Defervesced on or before day 4 2. No more than 1 further fever spike until visit 3. No tachypnoea and decreased work of breathing 4. No additional antibacterials given Dichotomous	Logistic regression
Secondary, between-group comparisons			
Absenteeism (caregiver, from work)	Short-course treatment is non-inferior to long-course treatment	Daily symptom diaries: self-reported number of caregiver-days absent from work (count)	Poisson regression
Absenteeism (child, from daycare/school)	Short-course treatment is non-inferior to long-course treatment	Daily symptom diaries: reported number of child-days absent from daycare/school (count)	Poisson regression
Mild drug adverse reactions	Fewer in short-course arm than in long-course arm	Daily symptom diaries: Reported number of child-days with diarrhoea, rash, abdominal pain, yeast infection (count)	Poisson regression
Anaphylaxis and other severe drug adverse reactions	Fewer in short-course arm than in long-course arm^a^	Daily symptom diaries, SAE reports. Dichotomous	Descriptive statistics

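### Poisson regression is named for the diary day counts with no allowance for overdispersion; for mild adverse-reaction days the error rate would probably exceed the nominal 5%

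*Protocol article*

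**What the plan says.** The Analysis section of the protocol article assigns one model family to each type of outcome; for counts it is "Poisson regression for count outcomes". Table 1 repeats this for three secondary outcomes taken from the daily diary:

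- caregiver absence, "self-reported number of caregiver-days absent from work (count", with a non-inferiority hypothesis;
- child absence, "reported number of child-days absent from daycare/school (count", with a non-inferiority hypothesis;
- mild drug adverse reactions, "Reported number of child-days with diarrhoea, rash, abdominal pain, yeast infection (count", with the superiority hypothesis "Fewer in short-course arm than in long-course arm".

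The section on safety and adverse events says that caregivers fill in a "symptom diary form each day post-randomization until the tenth post-randomization day", so each count is bounded at about 10 days. Every result is to carry an estimate, a 95% confidence interval and a p value, and "The criterion for statistical significance will be set at alpha = 0.05". The article mentions no scale parameter, robust variance, negative binomial model or zero-inflated model. The sensitivity analyses in Table 1 are limited to the primary outcome. No mean, standard deviation, share of zeros or episode length is given for any count.

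**The concern.** Poisson regression with model-based standard errors takes the variance of a child's count to equal its mean. That would be reasonable if each day were a separate, independent event. Days of diarrhoea or rash are not: one episode usually covers several consecutive days in the same child, while other children have none. Both features push the variance above the mean, and the model would then overstate its precision.

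The outcome most exposed is the one with a superiority claim. Fewer adverse reactions is one of the article's stated reasons for wanting a shorter course. A falsely significant result there would lend support to 5 days of treatment that the data do not give. For the absence counts, an interval that is too narrow would make a non-inferiority conclusion too easy, and one that is too wide would make it too hard.

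**Working it through.** **Inputs from the article.** 135 children per arm (Sample size); counts limited to 10 days (Safety and adverse events); alpha 0.05, taken as two-sided because 95% intervals are reported (Analysis). The article states no figure for the count outcomes that could be reproduced. Its only related figure is the primary sample size: with 5% failure in both arms, margin 7.5 points, one-sided alpha 0.025 and 80% power, (1.960 + 0.842)² × 2 × 0.05 × 0.95 / 0.075² = 133 per arm, close to the stated 135. So 135 per arm is used below.

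**Step 1: effect of dispersion on the test.** Let φ = variance/mean. The Poisson standard error of the log rate ratio is √(1/S₁ + 1/S₂), where S₁ and S₂ are the total days in each arm. The correct one is larger by √φ. The actual two-sided error is 2 × (1 − Φ(1.96/√φ)), and half of it falls in the direction that favours 5 days.

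| φ (assumed) | correct CI wider by √φ | two-sided error | error in the favourable direction (nominal 2.5%) |
|---|---|---|---|
| 1.5 | 1.22 | 11% | 5.5% |
| 2 | 1.41 | 17% | 8.3% |
| 3 | 1.73 | 26% | 12.9% |
| 4 | 2.00 | 33% | 16.4% |
| 5 | 2.24 | 38% | 19.0% |

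**Step 2: what φ could be.** If a share p of children has any day, and the days among those affected have mean μ and variance σ², then φ = σ²/μ + μ(1 − p). For geometric durations, before the 10-day limit, σ² = μ(μ − 1), so φ = (μ − 1) + μ(1 − p). Example: p = 0.3 and μ = 2 give φ = 1 + 1.4 = 2.4. The mean is then 0.6 day, so 135 children give 81 days per arm, and the Poisson standard error is √(2/81) = 0.157. An observed rate ratio of 1 would be reported with an interval of 0.73 to 1.36; with √2.4 = 1.55 applied, it is 0.62 to 1.61.

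**Step 3: simulation with no true difference.** 135 per arm, 5,000 trials per scenario, counts capped at 10, geometric or shifted-binomial durations. All distributions are assumptions.

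| Outcome, share with any day, mean days in those affected | φ | two-sided error, model-based Poisson |
|---|---|---|
| Adverse reactions, 20–50%, 2–4 days | 1.4 to 5.1 | 10% to 39% |
| Adverse reactions, 20–50%, 1.5 days | 1.07 to 1.7 | 6% to 13% |
| Absence, 80–100%, 1.5–4 days | 0.3 to 2.8 | near 0% to 25% |

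With an empirical (robust) variance the error is 4.4% to 6.2% in every scenario. A separate simulation of 4,000 trials, with 30–75% zeros, gave Poisson errors of 17.3%, 30.2% and 37.3% at φ = 2.14, 3.47 and 4.86, against 5.0%, 5.5% and 4.8% with robust variance. The formula in step 1 gives 18%, 29% and 37% at these φ.

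**The case against.** The strongest reply is that the article names a model family and does not say how the variance is estimated. Poisson regression with a sandwich variance is still Poisson regression, and a statistical analysis plan that is not shown may specify it. A reader might infer that the trial is committed to variance equal to the mean; the text does not go that far, so the error rates above are conditional on model-based standard errors. The point survives because the method is stated, twice, with no qualification, for outcomes it does not suit as written.

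A reader might also infer that the intervals are far too narrow for all three outcomes. The documents do not support this. They give no dispersion and no share of zeros. All participants are febrile children with pneumonia, so most may miss some daycare or school, or cost a caregiver some work. The absence counts could then be near-Poisson or underdispersed and the intervals too wide. Even for adverse reactions, short episodes (mean 1.5 days) would bring the error down to 6–13%.

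A third inference is that counting from day 1 is itself an error, because "All study participants will begin the study receiving high-dose amoxicillin divided into three times daily and given orally for 5 days" and the arms can differ only afterwards. Suppose both arms have 1.0 day in days 1–5, followed by 0.5 versus 1.0 day. The ratio is 1.5/2.0 = 0.75 over the whole period and 0.5/1.0 = 0.50 from day 6, but the saving is 0.5 day either way. Total burden from enrolment is a legitimate outcome and 0.75 is its correct ratio. For the adverse-reaction test, this dilution moves the ratio towards 1, so it cannot create a false superiority claim.

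**Conclusion.** The point holds for mild adverse-reaction days. Variance above the mean is likely there, and for an assumed φ of 1.5 to 5 the superiority test would have two to nearly eight times its nominal error if model-based standard errors were used. For caregiver and child absence, only the unknown direction can be stated: model-based intervals may be too narrow or too wide. Every size given here rests on assumed distributions and on the standard errors being model-based. These are secondary outcomes, so the primary non-inferiority conclusion and the 270-participant target do not depend on this. It is still worth correcting, because the adverse-reaction result would be used to argue for the shorter course.

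**What to change.** In the Analysis text and the three Table 1 rows, replace the Poisson entry by Poisson regression with robust (sandwich) variance, adjusted for site, since randomisation is stratified by site. Negative binomial regression is an acceptable alternative where counts are overdispersed, but it does not handle underdispersion. Robust variance is therefore the safer single choice for all three outcomes. Settle the choice before unblinding. If an analysis plan already specifies robust variance, it is enough to align Table 1 with it.

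A count from day 6 onward, with the day 1–5 count as a covariate, may be added as a supportive analysis. It should not replace the whole-period outcome, because that would change what is being estimated.

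The cost is wording only, with no extra data. Intervals for adverse-reaction days will probably be wider, so a real reduction will be harder to show; those for absence may move either way.

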**Methods:**

The objective of this multicentre, randomized, non-inferiority, controlled trial is to investigate whether 5 days of high-dose amoxicillin is associated with lower rates of clinical cure 14–21 days later as compared to 10 days of high-dose amoxicillin, the reference standard. Recruitment and enrolment will occur in the emergency departments of McMaster Children’s Hospital and the Children’s Hospital of Eastern Ontario. All children in the study will receive 5 days of amoxicillin after which point they will receive either 5 days of a different formulation of amoxicillin or a placebo. Assuming a clinical failure rate of 5% in the reference arm, a non-inferiority margin of 7.5%, one-sided alpha set at 0.025 and power of 0.80, 270 participants will be required. Participants from a previous feasibility study (n = 60) will be rolled over into the current study. We will be performing multiplex respiratory virus molecular testing, quantification of nasopharyngeal pneumococcal genomic loads, salivary inflammatory marker testing, and faecal microbiome profiling on participants.

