### Statistical analysis

#### Sample size

We estimate the baseline failure rate of standard therapy to be ~ 5%; this estimate is consistent with previous studies in children [13], is less than in similar adult studies [7], and is the approximate rate that was seen in the pilot study. We will use a non-inferiority margin of an additional 7.5%. As this is a non-inferiority trial, the crucial statistical comparison will be between the 97.5% (one-sided) CI of the difference between the failure rate of the experimental arm and the standard therapy arm; should the upper bound of this difference be smaller than 7.5%, a conclusion of non-inferiority will be reached. As the maximum baseline failure rate in the reference arm is probably 5%, the maximum failure rate in the experimental arm that would still be felt to be “non-inferior” would be 12.5%; the margin of 7.5% was selected to make the maximum failure rate in the experimental arm less than 13.5%, the median acceptable failure rate in the treatment of CAP identified in a survey of infectious-disease physicians [37]. Setting α at 5%, with 80% power, 135 participants in each arm will be required for this trial (PASS software package, NCSS LLC, Kayesville, UT, USA); as we will have accrued ~ 60 subjects in the pilot to be “rolled over”, an additional 210 participants will be required. Our experience conducting the pilot, combined with an analysis of visits to the EDs of the study sites, leads us to believe that this target should be achievable. It is estimated that the target sample size should be attainable after 2 years of enrolment.

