Adherence to study medications	Better in short-course arm than in long-course arm	Daily symptom diaries, RA interview: “adherence” defined as > 80% amoxicillin doses given (<3 doses of initial 15 doses in short-course arm, < 6 doses in reference arm) Dichotomous	Logistic regression
Recurrence of respiratory illness after primary outcome visit but before 30-day follow up	Short-course treatment is non-inferior to long-course treatment	RA interview. Dichotomous	Logistic regression
Development of antibiotic-resistant organism (ARO) colonization	Less frequent in short-course arm than in long-course arm	Enteric swab testing: “new colonization”’ defined as 3–6 month swab ARO positivity in context of baseline swab ARO negativity. Dichotomous	Logistic regression
Disruption of gut microbiome	Less marked in short-course arm than in long-course arm	Enteric swab testing: comparison of gut microbiome at 3–6 months to baseline gut microbiome. Continuous	Linear regression
Tertiary, entire-cohort			
Distribution of salivary C-reactive protein in cohort	Mean will be greater than that observed in children with bronchiolitis but less than that observed in children with empyema	Salivary swab testing: continuous	Descriptive statistics expressed as mean (95% CI)
Prevalence of high-level *S. pneumoniae* nasopharyngeal colonization	Majority of cohort will be positive	Nasopharnygeal swab (NPS) testing: Dichotomous	Percentage, with 95% CI
Prevalence of *Mycoplasma* detection	Minority of cohort will be positive	NPS testing: Dichotomous	Percentage, with 95% CI
Subgroup analyses			
Older (age 5–10 years) vs. younger (age <5 years)	Older age group will have higher salivary CRP values, lower rates of *S. pneumoniae* high-level colonization, more *Mycoplasma* positivity, and decreased rates of clinical cure	Clinical cure (as defined above)	Logistic regression with an interaction term between subgroup and treatment variables
Higher vs. lower salivary CRP	Higher salivary CRP will be associated with decreased rates of clinical cure	Clinical cure	Logistic regression with an interaction term between subgroup and treatment variables
Virus/*Mycoplasma* detected in baseline NPS vs. no virus detected (for primary outcome)	Detection of a virus or *Mycoplasma* will not affect observed rates of clinical cure	Clinical cure	Logistic regression with an interaction term between subgroup and treatment variables
Sensitivity analyses – for primary outcome only			

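### With about 13.5 expected failures, the three planned logistic interaction models may yield no finite odds ratio or interval, because a treatment-by-subgroup cell can have no failures

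*Protocol article*

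**What the plan says.** The Analysis section of the protocol article states: "We will perform some subgroup analyses by adding an interaction term between treatment group (5-day vs. 10-day course) and the following subgroups", and lists age, salivary CRP, and virus or *Mycoplasma* detection. Each Table 1 row for these subgroups gives the same method: "Logistic regression with an interaction term between subgroup and treatment variables", with clinical cure as the outcome. On their status the plan is clear: "These interaction tests will be exploratory in nature and not adjusted for multiple testing".

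A later paragraph of the same section says that all analyses will be reported as an effect estimate with a 95% CI and a p value. It adds that evidence of effect modification will lead to further analyses.

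The number of events follows from the Sample size section: "We estimate the baseline failure rate of standard therapy to be ~ 5" per cent, and "135 participants in each arm will be required for this trial".

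**The concern.** A model with a binary treatment, a binary subgroup and their interaction has four parameters for four cells, so it reproduces the observed failure proportion in each cell. The interaction odds ratio is then a ratio of cell odds. If one cell has no failures, the ordinary maximum-likelihood estimate goes to zero or infinity. Software reports an arbitrary large coefficient with a huge standard error, and the promised estimate and interval cannot be given.

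What is at stake is limited but real. The Background section makes effect modification (by virus or atypical pathogen, pneumococcal load, CRP or radiograph) the secondary research question, and two of the three interaction models address part of it. A degenerate p value near 1 could be taken as absence of interaction and close off the follow-up analyses that the plan foresees.

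**Working it through.** **Inputs from the article**
- Failure rate 5% in the reference arm, taken as equal in both arms for the design (Sample size).
- Margin 7.5 percentage points: "We will use a non-inferiority margin of an additional 7.5" per cent (Sample size).
- "one-sided alpha set at 0.025 and power of 0.80, 270 participants will be required" (Abstract, Methods).
- Equal allocation: "half of the participants will take a second 5 days of amoxicillin" (Study interventions).

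**Reproducing the plan's sample size**

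n per arm = (1.960 + 0.842)² × 2 × 0.05 × 0.95 / 0.075² ≈ 133, against 135 stated. The 5% rate and the 135 per arm therefore belong together and can be used for the event count.

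**Expected failures**

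270 × 0.05 = 13.5, or 6.75 per arm. With an even subgroup split this is 13.5 / 4 ≈ 3.4 per cell.

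**Chance of at least one empty cell, per model**

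With n1 and n2 children per arm in the two subgroups and a common failure rate of 5%:

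P = 1 − [(1 − 0.95^n1)(1 − 0.95^n2)]²

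| Minority share | n1, n2 per arm | 0.95^n1, 0.95^n2 | P |
|---|---|---|---|
| 50% | 67.5, 67.5 | 0.031, 0.031 | 0.12 |
| 40% | 54, 81 | 0.063, 0.016 | 0.15 |
| 25% | 34, 101 | 0.175, 0.006 | 0.33 |

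The shares are assumptions, because the article states none for the interaction models. Two figures elsewhere make a share near 25% plausible without establishing it. The 75th percentile of CRP is the cut for a different, stratified sensitivity analysis. The 73% virus detection quoted in the Discussion comes from inpatients with severe pneumonia and would leave about 27% virus-negative.

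**Sensitivity to the assumptions**
- *Missing specimens.* Participants may decline any specimen. If 20% lack data (assumed), 108 per arm remain. Even split: 1 − (1 − 0.95^54)⁴ = 0.23. At 25%: 1 − [(1 − 0.95^27)(1 − 0.95^81)]² = 0.46.
- *Minority subgroup fails twice as often, 25% share, 5% overall.* The rates are 0.05 / (0.25 × 2 + 0.75) = 4% and 8%. P = 1 − [(1 − 0.92^34)(1 − 0.96^101)]² = 0.14.
- *Minority subgroup fails half as often, 25% share.* P = 0.61.
- *Failure rate 7.5% in the 5-day arm.* P = 0.07 at an even split and 0.24 at 25%.

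**At least one of three models**

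The same failures enter all three models, so the models are not independent. Simulation with 135 per arm, 5% failures in both arms and independent subgroup memberships gives about 0.27 with three even splits, and 0.55 with assumed shares of 35%, 25% and 30%.

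**What an empty cell does to the output**

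Illustrative data: failures 5/95 and 2/40 in the 10-day arm, 7/95 and 0/40 in the 5-day arm. The ordinary fit gives an interaction coefficient of about −21 with a standard error of about 12,564 and a Wald p of 0.999. The likelihood-ratio test on the same data gives p = 0.074. The test survives; the estimate and a finite interval do not.

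**The case against.** The strongest objection is that sparse-cell handling in an exploratory model is normally left to the statistical analysis plan, which is not shown, and that Firth-penalised regression is itself a form of logistic regression and would comply with Table 1. This stands in part, and it keeps the point minor. It does not remove it: Table 1 names a method, the Analysis section promises a specific output, and under the plan's own event count the usual form of that method may not deliver it.

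Three stronger readings are tempting and are not supported.
- A reader might infer that the plan relies on Wald tests, so that the interaction tests themselves fail. The article names no type of test, and a likelihood-ratio test from the same model remains usable.
- A reader might infer that the method fails in about half of trials. That figure needs particular assumed shares and equal failure rates. Table 1 itself hypothesises lower cure in older children and with higher CRP; if the higher-risk group is the smaller one, the chance falls, as in the 14% case. If it is the larger one, the chance rises.
- A reader might take the sentence on multiple testing to be the fault. It concerns multiplicity and is unobjectionable; it matters here only because it declares the tests exploratory.

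It is also fair to say that an analyst would probably notice a standard error in the thousands. That lowers the risk of misreading but does not supply the missing estimate.

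**Conclusion.** The point holds as a minor one. For each interaction model, the chance that ordinary logistic regression has no finite odds ratio and interval is about 12% at an even split and 33% at a 25% share, given 135 per arm and 5% failures in every cell. Across the variations examined at these two shares it runs from 7% to 61%. For at least one of three models it is about 27% to 55% under the stated shares. All of these figures depend on subgroup shares, specimen completeness and failure rates by subgroup that the article does not give. The non-inferiority conclusion is not touched.

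**What to change.** In the three subgroup rows of Table 1, specify Firth-penalised logistic regression with profile-penalised-likelihood intervals and tests for the interaction. This gives a finite estimate and a usable p value when a cell is empty. If the statistical analysis plan already contains a sparse-data rule, the two documents only need to agree.

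The cost is a line of analysis wording, standard software and slight shrinkage of the estimates. Nothing in conduct or sample size changes. The fix does not add power: with about 13.5 failures, the interaction estimates will be imprecise under any method, and the report should say so. Subgroup risk differences set against the 7.5-point margin are a separate preference and are not needed to resolve this point.
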